### **1.2 Sponsor**

Technical University Munich, University Hospital “Rechts der Isar”

(Note: the Coordinating Investigator will become Head of the Dept. of Psychosomatic Medicine in Munich from September 2005)

### **1.5 Name, title, address, and telephone number(s) of the qualified physician who is responsible for all trial-site related medical decisions (if other than investigator)**

Does not apply, as local investigators are responsible for trial-site related medical decisions.

## **2. Background Information**

### **2.1. Name and description of the intervention**

Psychodynamic-interpersonal psychotherapy for patients with pain predominant multisomatoform disorder in different somatic specialities

PISO will test a specific form of psychotherapy which is adapted to the needs of patients who complain persistently about bodily symptoms like pain and bodily dysfunction for which no adequate organic explanation can be found. These patients typically turn for help to somatic specialists like pain treatment centers run by anaesthetists or orthopaedic surgeons, departments of neurology or internal medicine. Typically they reject psychosocial explanations for their symptoms and therefore are not motivated to enter into classical psychotherapy. Hence psychotherapeutic strategies have to be developed that are acceptable to this patient group as a whole and not only to the few selected ones who are motivated enough intrinsically or extrinsically to seek help in a psychotherapeutic/ psychosomatic/ psychiatric institution on their own.

The intervention tested in PISO is based on the principles of short term psychodynamic-interpersonal psychotherapy (PIT). This is a modern type of psychodynamic psychotherapy that has been shown to be effective in different populations and settings (Leichsenring et al. 2004). The specific application to patients with somatoform disorders is based on adaptations of psychodynamic-interpersonal therapy as developed by Guthrie in the UK and Rudolf and Henningsen (2003) in Germany.

### **2.2. Summary of findings from preclinical studies and previous clinical trials/ studies/ clinical standards**

Three of the investigators, with the coordinating investigator as principal author, were members of the group who established evidence-based practice guidelines on the diagnosis and treatment of somatoform disorders for the German Association of scientific medical societies (AWMF). These guidelines won the DKV-Cochrane prize (€ 25.000.-) in 2000 for distinguished contributions to evidence based medicine. Updated guidelines were published in 2002 (Henningsen et al. 2002). The guidelines are based on a systematic review of the evidence base for the treatment of somatoform disorders. More than 3000 articles were screened and the relevant primary studies were extracted in tables. The literature that appeared since 2002 was searched systematically in November/ December 2004 using the same search strategy that was used for the guidelines and the first update.

Based on these data psychotherapy has been shown to be effective in so-called functional somatic syndromes, with best evidence being available for Cognitive-Behavioural Therapy for Chronic Fatigue Syndrome and Hypochondriasis and for Psychodynamic-Interpersonal Therapy for functional gastrointestinal disorders. Effectiveness in these studies relates to reductions in the intensity of physical symptoms and improvements in quality of life.

However, two problems currently limit the validity and usefulness of treatments in this field:

On the one hand, patients with medically unexplained bodily symptoms typically see themselves as physically ill and when being sent to a psychiatrist/ psychotherapist or being offered usual psychotherapy, only a selected sub-group will accept this.

On the other hand, trials that address unselected patients directly in medical specialities have so far been confined to examining efficacy and effectiveness in specific functional somatic syndromes (FSS) like irritable bowel syndrome or fibromyalgia only. This may not be the best paradigm for evaluating the effectiveness of such treatments in somatization, as the evidence for specific discrete FSS is weak. They display a wide overlap of symptoms and share many non-symptom characteristics like association with depression and anxiety and similar response to non-pharmacologic and pharmacologic treatments (Wessely et al. 1999, Barsky and Borus 1999).

### **2.3. Risks and benefits, if any, to human subjects**

#### **Benefits**

According to our main hypothesis patients from somatic speciality clinics who fulfill diagnostic criteria for multisomatoform disorder with predominant pain symptoms and who receive manualized psychotherapy based on PIT principles will show improved quality of life (QoL) in comparison to controls who receive enhanced medical care. Furthermore, according to the secondary hypothesis on a psychobehavioural level, patients with multisomatoform disorder in somatic speciality clinics who receive manualized psychotherapy will show reduced health care utilisation, less physical symptoms and more adaptive illness representations and higher levels of emotional awareness compared to controls.

#### **Risks**

As it is based on common therapeutic strategies in patients with medically unexplained symptoms, the intervention in PISO is not experimental. Psychotherapeutic interventions like this have repeatedly been shown to be relatively safe, but all have potential side effects. In particular, there is a risk that during the intervention patients may transiently become more depressive and/ or suicidal as a sign of altered emotional processing of life stresses. Close monitoring of this risk by the therapist is assured through the PIT manual and is helped by the fact that the intervention is taking place not in group, but in single patient format. Appropriate action (e.g. antidepressive medication, psychiatric in-patient referral) is defined in a manual for clinical care that will be adapted to the local situation of each centre.

### **2.4. Description of and justification for the route of administration/ method/ intervention**

When left untreated, a majority of frequently attending patients with medically unexplained symptoms continues to be incapacitated by their symptoms even after three years (Gureje and Simon 1999, Reid et al. 2003). The evidence base for the effectiveness of other, in particular psychopharmacological, treatments is weaker than for psychotherapeutic ones. A systematic evaluation of manualized short-term PIT which is aimed at patients in somatic speciality settings, transcends the diagnostic constraints of single functional somatic syndromes and allows easy transfer to daily clinical praxis is lacking up to now.

### **2.5. Statement that the trial will be conducted in compliance with the protocol, GCP and the applicable regulatory requirement(s).**

PISO will be conducted in compliance with the protocol, GCP and the applicable regulatory requirement(s).

### **2.6. Description of the population to be studied**

The PISO trial focuses on patients with pain predominant multisomatoform disorder. Multisomatoform disorder (MSD) is a diagnostic construct proposed by Kroenke et al. (1997) for a moderate severe disorder of three current and a history of at least two years of organically unexplained bodily symptoms and severely reduced quality of life that appears to be more appropriate to describe patients with medically unexplained bodily symptoms than other diagnoses like somatization disorder. Empirically, pain is the most frequent type of complaint, followed by functional complaints and fatigue.

Patients with these symptoms typically see themselves as physically ill and therefore tend to consult somatic specialists like neurologists, pain therapists or specialists for internal medicine. Taking this into account, patients with multisomatoform disorder will be recruited in different somatic speciality wards or outpatient clinics, thereby avoiding the selection effects which are operative when treating patients who come to psychosomatic/ psychiatric departments directly. Therapy will be performed as outpatient treatment only.

## 3. Trial Objectives and Purpose

Severe symptoms of pain and bodily dysfunction that remain medically unexplained after appropriate investigation are very frequent in primary care and in most medical speciality clinics, with frequencies of between 30-40% for gastroenterology and neurology and up to 66% for gynaecology (Nimnuan et al. 2001, Reid et al. 2001). In the German general population, lifetime prevalence for pain-dominant somatoform disorders is 33.7%, for those that significantly impair functioning it is 12.3% (Grabe et al. 2003). Psychiatric morbidity is high, and many patients have chronic psychosocial problems. The dysfunctional behaviour of such patients is often maintained by fixed illness representations that signify organic disease despite reassurance to the contrary by multiple physicians. Patients with medically unexplained bodily symptoms are so-called "high utilizers" of the health care system, incurring costs that are up to 10 times higher than in average patients (Bass 2001). Even patients not fulfilling diagnostic criteria for somatization disorder proper are severely functionally disabled by their organically unexplained symptoms (Kroenke et al. 1997, Dickinson et al. 2003). When left untreated, a majority of frequently attending patients with medically unexplained symptoms continues to be incapacitated by their symptoms even after three years (Gureje and Simon 1999, Reid et al. 2003).

Multisomatoform disorder (MSD), a diagnostic construct proposed by Kroenke et al. (1997) for a moderate severe disorder of three current, a history of at least two years of organically unexplained bodily symptoms and severely reduced quality of life appears to be more appropriate to describe these patients. In concentrating on current bodily symptoms, this diagnostic construct avoids the instability demonstrated in somatization diagnoses that are based on lifetime symptoms like somatization disorder (SD) or abridged somatization disorder (ASD) (Dickinson et al. 2003).

Building on our previous work we want to a) examine the effectiveness of PIT in patients with pain predominant multisomatoform disorder in different somatic specialities like anaesthesiological pain treatment centres, neurological, dental and internal medicine departments and b) test a biopsychosocial model of change in which improvements particularly in disability and physical symptoms will be mediated by changes in illness representations and in heart rate variability in a stress-task paradigm.

## 4. Trial design

### 4.1. Primary and secondary endpoint

#### Primary endpoint

The primary purpose of this study is to assess if patients who fulfil diagnostic criteria from multisomatoform disorder with predominant pain symptoms and who receive manualized psychotherapy based on PIT principles (test group) will or will not show improved quality of life in comparison to controls who receive enhanced medical care (control group). The primary analysis will be based on the German version of the SF-36 Health survey short form (Bullinger and Kirchberger 1998). The statistical hypothesis will be based on the Physical Component Score of SF- 36. (t 0, t 1, t 2)

Statistical hypothesis:

H0: *no treatment difference between control and test group*

vs.

H1: *difference between control and test group*

#### Secondary endpoints

- **IPQ, Brief Form**

The brief form of the „Illness Perception Questionnaire“ (BIPQ, Broadbent et al. in submission) provides a quantitative measure of the components of illness representations (identity, consequences, timeline, personal control, treatment control, emotional representations, illness coherence, psychological attributions, risk factor attributions) that has been shown in treatment trials to be sensitive to change. The German version was developed and validated by Gaab (unpublished manuscript) (t 0, t 1, t 2).

- **PHQ-D**

The „Patient Health Questionnaire“, German version (PHQ-D) is a brief self-report measure for anxiety, depression and other mental disorders. Criterion validity was established with respect to diagnostic gold standards and the PHQ has proven to be a responsive and reliable measure of depression treatment outcome (Löwe et al. 2004) (t 0, t 1, t 2).

- **SOMS-7**

Seven-day version of the „Screening for Somatoform Symptoms“. A 53-item instrument for the evaluation of treatment effects in somatoform disorders, covering all somatic symptoms occurring in somatization disorder, according to DSM-IV and ICD-10 (Rief and Hiller 2003)(t 0, t 1, t 2).

- **Whiteley-Index-7**

The seven-item version of the Whiteley Index, an established hypochondriasis scale first described by Pilowsky, was developed and validated by Christensen et al. (2003) specifically to assess treatment effects. (t 0, t 1, t 2)

- **TAS**

The „Toronto Alexithymia Scale“ (Bagby et al. 1994) is a 20-item self-report measure of alexithymia with good internal consistency and test-retest reliability and a factor structure congruent with the alexithymia construct (t0). Alexithymia is conceptually related to expected effects of the treatment intervention and will be therefore assessed as a predictor variable.

- **ECR**

The Questionnaire „Experiences in Close Relationships“ (ECR, Brennan et al. 1998, german adaption: the Bochum Adult Attachment Questionnaire, Neumann et al., submitted) measures the two attachment dimensions avoidance and anxiety to characterize the quality of partner attachment (t0).

- **HAQ**

The „Helpful Alliance Questionnaire“ (Luborsky 1984, German Version: Bassler et al. 1995) is a brief (12 Items) questionnaire for the assessment of perceived therapeutic relationship and therapeutic process. It will be answered as well by the patient as by the therapist and allows interpretation of potentially relevant moderators of therapy outcome (t1).

- **Heart rate variability**

HRV measurement and analysis equipment will be present at each centre. Time-domain (RMSSD) and frequency domain (HF-HRV) analysis will be performed during a stress test

with the emotional stroop paradigm (detailed description of methods see Supplement 5). (t 0, t 1, t 2)

#### **4.2 Description of the type/design of trial to be conducted**

Multi-centre two-arm randomized controlled trial with major end point at follow-up at 1 year, the guidelines of Good Clinical Practice (GCP) will be followed, reporting will follow the CONSORT rules.

A schematic diagram of the trial design, procedures and stages can be found in Supplement 2 of this Protocol.

#### **4.3 A description of the measures taken to minimize/ avoid bias (randomization, blinding)**

- Blinding of patients and treatment is not possible in the trial.
- Primary and most secondary endpoints are self-report measures. However, assessors will be scientific assistants from other parts of the respective trial sites who are not involved in the trial and blinded as to the treatment of the patient. As a check, they will be asked to guess the respective status of patient. Patients will be asked to withhold details of treatment from investigators and not to include intervention sessions in their health care utilisation interview..
- Potential participants will be screened consecutively in the co-operating somatic departments which are chosen for high base rates in patients with pain-dominant medically unexplained symptoms. All patients present in the respective unit for whom obvious exclusion criteria like severe organic disease or insufficient language ability do not apply will be informed about the study and asked to take part in an assessment of eligibility including the SOMS-7, the SF-36 and, if beyond cut-off, a diagnostic gold-standard interview (excerpt from SCID-1, adapted to test for criteria of MSD, see Henningsen et al. 2005).
- All therapy sessions will be audiotaped. Integrity of therapy will be monitored through regular supervision and independent rating of a random sample of audiotapes (2 sessions/ therapy) using the Sheffield Psychotherapy Rating Scale (Startup and Shapiro 1993). Therapists will fill out the adherence scale after every second session in order to prevent drift.
- Only therapists experienced in the use of psychodynamic-interpersonal psychotherapy will take part in the study. All therapists will be trained together in the application of the treatment manual in a central workshop before starting the treatment period; booster training sessions will aim at maintaining and further increasing therapist adherence.
- Patient's use of medications and other therapies will be monitored. For additional treatment decisions during the intervention, patients will be referred to their General Practitioner

#### **4.4 Description of the trial treatment and the dose of the intervention**

##### **Experimental Intervention**

Manualized phase –defined 12 session intervention based on the principles of psychodynamic-interpersonal psychotherapy (Rudolf and Henningsen 2003, Margison 2002) applied to the purposes of patients with organically unexplained bodily symptoms (Guthrie et al. 1999)

Phase 1: Build-up of therapeutic relationship through symptom-oriented exploration and psychoeducation.

Phase 2: Broadening of the patient's explanatory model and symptom management.

Phase 3: Clarification of interpersonal symptom contexts and accompanying affects/ emotions.

Phase 4: Termination and transfer, including a detailed farewell letter.

The manualized intervention is adapted in Phase 1 to the leading symptom of the patient, otherwise it is identical across somatic specialities. The manual also defines the rules for taking part in parallel somatic treatments.

(For an extended English summary of the manual see Supplement 3a)

##### **Control Intervention**

Enhanced medical care for the respective symptom leading to current health care utilisation.

All patients are treated at specialized university departments, thereby assuring up to date treatment according to established guidelines. In addition to “treatment as usual” they will take part in three monthly protocol-defined case management counselling interviews aimed at increasing self care skills and shared decision making in illness behaviour. Patients assigned to ‘enhanced medical care’ will be informed of their research diagnosis and encouraged to inform their physician of their diagnosis, allowing them and their physicians to initiate primary care or speciality treatment without restrictions.  
(for an English version of the guideline on “Enhanced Medical Care” see Supplement 3b).

**Interpretation of differences between study arms concerning type of intervention and time spent with the patient**

The design of the trial incorporates a confounding of type of intervention and time spent with the patient. Hence, this design does not control for unspecific effects of time spent with the patient. As a result, we will not be able to confirm the specificity of psychodynamic-interpersonal therapy for the treatment of patients with MSD.

This is acceptable because a) the main aim of the trial is a pragmatic one: is there anything effective that can help such patients as there is such limited evidence for effectiveness? If there is sufficient evidence that this treatment is beneficial, specificity can be addressed in later studies. b) To confirm specificity would involve a more elaborate and costly design, ideally a three limbed study PIT vs counselling vs. enhanced medical care. For one type of functional somatic syndrome, PIT has already been shown to be specific (Hamilton et al. 2000).

**4.5 Expected duration of subject participation and description of the sequences and duration of all trial periods, including follow-up**

The expected duration of subject participation is 16 months overall: A 4-week-period for screening, randomization and pre-therapy investigation, a 12-week-period for 12 weekly sessions of manualized psychodynamic-interpersonal psychotherapy or control intervention, final assessment after three months and follow-up-investigation 12 months after completion of therapy.

(For more details of trial schedule see trial diagram, Supplement 2)

**4.6 Description of the „stopping rules“ or „discontinuation criteria“ for individual subjects, part of trial and entire trial**

There are no predefined statistical stopping rules and no interim analyses in this trial.

Premature study termination can be due to the following reasons:

- Trial Steering or Data Monitoring and Safety Committee recommend to stop the trial
- Risk-benefit ratio is changed in relevant degree (e.g. through new external information)

A study site can be closed prematurely for the following reasons:

- Major protocol violations
- Inadequate patient recruitment
- Non-Compliance to the study requirements

For criteria for individual subject withdrawal see 5.3

**4.7 Accountability procedures for the intervention, including the placebo(s) and comparator(s), if any**

Does not apply in this trial.

**4.8 Maintenance of trial treatment randomization codes and procedures for breaking codes.**

Randomized allocation to one of two treatment arms after assessment of eligibility, and after obtaining informed consent from the patients for participation.

The patients selected for participation will be randomly assigned to either the control (enhanced medical care) or intervention group (manualized psychotherapy based on PIT principles) by a computer generated multi-block randomization schedule using the program “Rand”. This randomization schedule will be generated at the Coordination Centre for Clinical trials. The schedule will be a 1:1 ratio, permuted in setting blocks of 4, 6 and 8 patients. Randomization

will also be stratified by participating hospitals and settings. The concealment of treatment allocation is ascertained through central allocation in the KKS Düsseldorf by fax. The trial is not blinded to patients or staff treating them as this is impossible with the intended trial design.

**4.9 Identification of any data to be recorded directly on the CRFs (i.e. no prior written or electronic record of data), and to be considered to be source data.**

The primary outcome and the majority of secondary outcomes are self report questionnaires that are considered to be part of the case report forms.

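### Section 4.8 prints the exact block sizes of a stratified, open-label trial, so site staff who track their own stratum could deduce a few upcoming allocations despite central fax allocation

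*Protocol*

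**What the plan says.** Protocol section 4.8 states the ratio and the block sizes in one sentence: the schedule is 1:1, "permuted in setting blocks of 4, 6 and 8 patients". The schedule is called a "computer generated multi-block randomization schedule using the program" Rand. Randomisation "will also be stratified by participating hospitals and settings". Section 4.8 does not say how the three sizes are ordered or mixed within a stratum.

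The same section says that "The trial is not blinded to patients or staff treating them as this is impossible with the intended trial design". Concealment rests on one measure: "The concealment of treatment allocation is ascertained through central allocation in the KKS Düsseldorf by fax". Allocation comes after eligibility assessment and consent.

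Under section 11.1 the monitor takes each investigator through the protocol, so the sites know what section 4.8 says. No section reserves the block sizes to the coordination centre.

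**The concern.** Central allocation stops site staff from reading the list. It does not stop them from reasoning about it. In an open trial, staff of a unit can learn which arm earlier patients entered. If they also know that every block has size 4, 6 or 8 and is balanced, some histories leave only one possible next allocation.

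Where the next arm is known, whoever approaches patients could bring one forward or hold one back. Randomising after consent does not prevent this, because the decision to approach comes earlier. The primary endpoint, the SF-36 Physical Component Summary, is self-reported by unblinded patients. A difference in prognosis or motivation created at entry would therefore pass into the treatment contrast. Blinded assessors (section 4.3) protect the assessment of outcome, not entry.

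**Working it through.** The plan gives no figure for predictability, so there is none to reproduce.

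**Inputs**
- Block sizes 4, 6, 8 and ratio 1:1: section 4.8.
- Sample size 2 × 88 = 176: section 9.2.
- Number of strata: the pilot table in section 9.3 lists six centres, three with one setting and three with two, so 3 × 1 + 3 × 2 = 9 hospital-by-setting cells. Taking these as the trial's strata, and as equal in size, is an assumption: 176 / 9 = 19.6, about 20 patients each.
- Assumed: each block size is drawn independently with probability 1/3, and the observer knows all earlier allocations in the stratum.

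**How an allocation becomes certain.** Suppose the first four patients of a stratum all go to arm A. A block of 4 holds only two A and a block of 6 only three, so the block must be of size 8, and the next four allocations must all be B. Counting either arm, the chance of this for a first block is 1/3 × 2/C(8,4) = 1/3 × 2/70 = 0.0095. Other histories also force allocations, so the total needs simulation.

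**Simulation.** Strata were generated at random, 8,000 per scenario. Before each patient, the exact posterior over block size and position was computed from the history. An allocation counts as certain if its posterior probability is 0 or 1.

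| Sizes drawn independently, 20 per stratum | Result |
|---|---|
| Certain | 2.4%; 0.024 × 176 ≈ 4 patients |
| Predictable with probability ≥ 0.90 | about 4%; 0.04 × 176 ≈ 7 patients |
| Strata with at least one certain allocation | 17.1% |
| Best guess correct, sizes known | 67.1% |
| Guessing the arm that is behind, sizes ignored | 67.1% |

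The chance that at least one of the nine strata contains a certain allocation is 1 − (1 − 0.171)^9 = 0.815. With 29 patients per stratum the certain share is again 2.4%.

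**Sensitivity to the order of sizes.** If 4, 6 and 8 were each used once per cycle of 4 + 6 + 8 = 18 patients, the third size would follow from the first two, and patient 18 would always be forced. The certain share would then be about 10% at 20 per stratum (0.10 × 176 ≈ 18), 11% at 18, 8% at 29, but only 3.7% at 16 and 2.6% at 10.

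**Possible effect on the endpoint (illustration only).** Suppose all 4 certain slots are exploited, two per arm, with patients 6.25 points (half the planned SD of 12.5) better in one arm and worse in the other. The bias is 2 × (2/88) × 6.25 = 0.28 points, against a planned difference of 6.25.

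**The case against.** The strongest objection is that printing the sizes adds little. Knowing them does not raise the average guess rate above 67.1%. That advantage comes from small balanced blocks within strata of an open trial, and deleting the sizes leaves it in place. This stands: the gain from withholding the sizes is confined to the certain and near-certain allocations.

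The protocol also has safeguards. Section 4.3 requires consecutive screening, with every patient present who has no obvious exclusion informed and asked. Eligibility then depends on questionnaire cut-offs and a structured interview. Section 4.8 places allocation after consent: "Randomized allocation to one of two treatment arms after assessment of eligibility, and after obtaining informed consent from the patients for participation". Section 11.2 has eligibility criteria and consent monitored completely. These limit steering but do not exclude it. Judging an obvious exclusion or a severe comorbidity leaves discretion, and monitoring of enrolled patients does not show who was deferred or not approached.

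Full sight of the stratum history is an assumption. Control care is given by physicians of the somatic units (Supplement 3b) and psychotherapy by trained therapists (section 4.3). The protocol does not say that a recruiter holds a complete, ordered record. With a partial record, fewer allocations can be deduced.

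A reader might infer that no analysis could help. That goes too far. Section 9.1 compares baseline data and allows covariates, and the endpoint is measured at baseline, so selection on measured factors could be detected and partly corrected. Selection on unmeasured prognosis or motivation could not.

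**Conclusion.** The point holds as a minor weakness in concealment. Under the stated assumptions (9 equal strata of about 20, independent and equally likely sizes, full knowledge of the stratum history), about 2% of allocations, about 4 of 176, are certain in advance and about 4% are predictable with at least 90% probability.

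Three stronger readings are tempting, and the protocol supports none of them.
- One could take the 10% from the 18-patient cycle as the size of the problem. Section 4.8 does not describe such a cycle, and the figure depends on strata reaching about 18 patients. It is a speculative upper case.
- One could read the wording as one fixed, known size per setting, which at 20 per stratum would make 33% (size 4), 23% (size 6) or 16% (size 8) of allocations certain. Section 4.8 does not say this either, and a multi-block schedule sits poorly with it.
- One could attribute the 67% guess rate to the disclosure, or conclude that allocation is generally known or the result biased. The guess rate is the same with the sizes withheld, and nothing in the protocol shows that selection would occur.

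**What to change.** Delete the block sizes from section 4.8 and from every document sent to sites. State only that permuted blocks of varying size, not disclosed to the sites, are used within hospital and setting. Hold the sizes in a restricted file at the coordination centre. If the list has not yet been generated, draw each block size independently at random, from a set other than the one already printed.

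The cost is one sentence in the protocol and, where still possible, generating the list with new sizes. Sample size and analysis are unaffected. The change removes certain deduction from known sizes; it does not remove the general advantage of guessing the arm that is behind.
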